### Sample size

A power analysis was conducted to determine the appropriate sample size. According to a previous RCT of MHL [32], assuming that we wanted to be able to identify a minimal difference of 0.18 effect size in MHL scores after the intervention. To detect differences in each group with one-way analysis of variance (ANOVA) that corresponds to a small effect size (0.18), with an alpha risk of 0.05, and a power of 80%, the adequate sample size required for this study in each group will be 85 students (*n* = 340). Assuming an attrition rate of 20% during the 12 months of follow-up after the intervention, we estimate that a total sample of 408 students will be required.

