### Recruitment process

The recruitment process for the trial began in September 2016. All eligible secondary schools within Barcelona city are contacted and encouraged to participate in the study. Emails providing information about the study are sent to all schools, and among those schools that had shown an interest in participating, a presentation is delivered at the school by two project researchers. Once a school agreed to participate, consent letters are sent out to the parents of all participating students.

Out of all the schools that accept participation in the study, a cluster randomisation by school and individual students as participants is conducted. The total sample estimated within a minimum of 408 adolescents will be divided into three experimental groups and one control waiting list. The randomisation assignment will be carried out through a computer program, and the group assignment will be 1:1:1:1.Each interviewer blinded the assessments.

Pre-treatment questionnaires will be completed approximately 2 weeks before the intervention by all students (intervention and control groups). A code will be used to match participant answers over time whilst preserving anonymity. One teacher will be the unique person responsible for keeping the identification number and corresponding student. Two researchers will be responsible for supplying each student with a questionnaire for its completion during each assessment within the study. The class teacher will be present in the classroom during the questionnaire administration involved in the data collection with the aim of minimising missing data and errors when providing the questionnaires.

A second evaluation will be performed approximately 2 weeks after the intervention. A third and fourth evaluation will be examined at 6 and 12 months, respectively. Table 2 shows the data collection and intervention programme timelines.

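### The attrition allowance multiplies 340 by 1.2 instead of dividing by 0.8, so 408 students leave about 326 completers at 20% loss, short of the required 340

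*Protocol article*

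**What the plan says.** The Sample size section of the protocol article sizes the trial with a one-way ANOVA across four groups, an effect size of 0.18, alpha 0.05 and power 80%. On that basis it states that "the adequate sample size required for this study in each group will be 85 students", and it gives the total as 340. It then moves from completers to recruits: "Assuming an attrition rate of 20% during the 12 months of follow-up after the intervention, we estimate that a total sample of 408 students" are needed. It names no other attrition rate and no other inflation rule.

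The same total is used as a recruitment floor in two more places. The Methods paragraph of the Abstract gives 408 as the least number to be recruited from 8 schools. The Recruitment process section says: "The total sample estimated within a minimum of 408 adolescents will be divided into three experimental groups and one control waiting list". That section also fixes allocation at 1:1:1:1, which makes 102 per arm.

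**The concern.** The section makes three statements: 340 students are needed, 20% will be lost, and 408 should be enrolled. They cannot all be true together. A dropout rate applies to the people enrolled, not to the people who must remain. Adding 20% of the required number therefore falls short of what is needed to absorb a 20% loss from the larger, enrolled number.

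The error runs in the anti-conservative direction, and there is no slack to absorb it, because 340 itself only just gives the stated power. A trial that recruited exactly its stated minimum and lost exactly its stated proportion would finish below its own requirement.

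**Working it through.** **Inputs, all from the Sample size and Recruitment process sections:** four groups, 1:1:1:1; one-way ANOVA; effect size 0.18; alpha 0.05; power 80%; 85 per group, 340 in total; attrition 20% by 12 months; total to recruit 408.

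**Step 1. Reproduce the 340.** The article does not name the metric of the 0.18, so Cohen's f is an assumption. Power is the probability that a noncentral F with 3 and N − 4 degrees of freedom and noncentrality λ = N × f² exceeds the 5% critical value of the central F.

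- N = 340: λ = 340 × 0.18² = 340 × 0.0324 = 11.02; power 79.9%.
- The smallest equal group size that reaches 80% is 86 (344 in total), so 85 reproduces to within one student per group.
- Reading 0.18 as a standardised difference between two means does not fit: it needs 485 per group two-sided, or 382 one-sided.

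The base of 340 therefore reproduces under the f reading. The slip is in the next step.

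**Step 2. Reproduce the 408.** 340 × (1 + 0.20) = 408 exactly.

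**Step 3. Apply the stated attrition to 408.**

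- Completers: 408 × (1 − 0.20) = 326.4, or 102 × 0.80 = 81.6 per arm.
- Shortfall in completers: 340 − 326.4 = 13.6, about 14.
- Attrition that 408 can absorb: (408 − 340)/408 = 68/408 = 16.7%.

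**Step 4. The total that meets the requirement.**

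- Overall: 340/(1 − 0.20) = 425, which is 17 more than 408 (17/408 = 4.2%).
- With equal arms: 85/0.80 = 106.25, rounded up to 107 per arm; 4 × 107 = 428, which is 20 more than 408.

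**Step 5. Effect on power, with f = 0.18.**

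| Completers | λ = N × 0.0324 | Power |
|---|---|---|
| 340 | 11.02 | 79.9% |
| 326.4 | 10.58 | 78.1% |

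The loss is 1.8 percentage points. Steps 2 to 4 do not depend on how the 0.18 is read; only the power figures do.

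**The case against.** The best case for leaving the figure alone is that it hardly matters.

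- **The effect is tiny.** Under two points of power, and a tolerance of 16.7% instead of 20%, lie well inside the uncertainty of a round-number guess at dropout. This stands, and it limits how much weight the point deserves. It does not make the stated total agree with the stated inputs.
- **408 is a floor.** The coding scheme in the article (8 schools, up to 6 classes, identification numbers up to 34) leaves room for more students, so 326 completers is what the minimum yields, not a forecast. That is fair. But a minimum is meant to be the lowest number that satisfies the requirement, and this one does not.
- **The shortfall concerns 12 months only.** The 20% is tied to the full follow-up, while the primary outcomes are also measured at 2 weeks and 6 months. Wherever loss is at or below 16.7%, 408 leaves at least 340. This stands and should be said.
- **Imputation is planned.** The Discussion mentions imputing missing subjects under intention to treat. Imputation does not restore the information lost with the outcomes, and the same paragraph accepts that losses may reduce power.
- **Clustering matters more.** The 340 comes from an individual-level ANOVA although schools are randomised. If the base is reworked for clustering, both 408 and 425 are superseded. That is true, and correcting this step does not settle the sample size as a whole. The division by 0.80 would still apply to whatever base replaces 340.

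**Conclusion.** The concern holds. The total of 408 does not deliver the required 340 at the assumed 20% attrition. It delivers about 326, a deficit of about 14 completers, or 17 recruits (20 with equal arms). That conclusion rests only on the article's own figures.

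The cost in power, from 79.9% to 78.1%, additionally assumes that 0.18 is Cohen's f and takes the individual-level ANOVA as given. No conclusion of the trial is likely to turn on it. It should still be corrected, because it is a demonstrable slip in the headline sample size and is stated three times.

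**What to change.** Choose one of two edits and make it in the Abstract, Sample size and Recruitment process sections.

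1. **Correct the total** to 425, or to 428 (107 per arm) so that the equal allocation holds with 85 completers in each arm. If 80% is to be reached strictly under the f reading, start from 344: 344/0.80 = 430.
2. **Keep 408 and restate what it gives:** about 326 completers at 12 months if 20% are lost, or 340 completers if loss does not exceed 16.7%.

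The second is a change of wording only. The first adds 17 to 22 students to a number already described as a minimum. Neither alters the conduct of the trial otherwise. Under either option, name the metric of the 0.18, and if the base of 340 is revised for clustering, apply the attrition allowance to the new base by dividing by 0.80.

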### Intervention

The *EspaiJove.net* programme started in 2010 and consists of: a) disseminating information on mental health; b) carrying out training activities with young people in schools; and c) carrying out training activities with professionals and families. The project is designed and delivered by professionals who are specialised in mental health and who move between different devices and educational centres to carry out training activities [30]. The programme includes education on several key aspects of mental health such as to: promote mental health wellbeing, facilitate help-seeking behaviours on their own, raise awareness of the consequences of risky behaviours, identify mental disorders and when/where to seek treatment, so as to eventually prevent and detect mental health-related problems early. Additionally, a person who has experienced mental illness first-hand will speak about his/her personal life experience with the students so as to aim to reduce any related stigma.

In this study we will asses three programmes (SP, MHL and MHL + SR) which consist of workshops run in the classrooms that cover the following topics:*Sensitivity programme (SP)* about mental health (1 h), including the concepts of mental health and mental disorders (emotional management).*Mental health literacy programme (MHL)* (6 h), including the contents of the EspaiJove.net programme. MHL programme module contents include: 1) Concepts of mental health and mental disorders. Mental health multidisciplinary team network; 2) Healthy and risky behaviours in mental health; 3) Social skills and antisocial behaviour, bullying and cyberbullying; 4) Anxiety, depression, self-harm, and suicidal behaviours; 5) Eating and behavioural disorders; 6) Substance abuse (alcohol and cannabis) and psychotic disorders.*Mental Health Literacy Programme plus Stigma Reduction* (*MHL + SR)* (7 h), including the six modules contained in the MHL programme and a presentation delivered by a person with first-hand experience of a mental disorder, accompanied by a voluntary member from the *Activament Catalunya Associació* (http://www.activament.org/es), a non-profit group specialised in reducing mental health-related stigma.

The intervention will be delivered by trained mental health nurses with vast experience in the treatment of children and adolescents. Nurses will receive previous training in relation to contents of the 6 modules of EspaiJove.net programme. The training period is 24 h (12 h theory and 12 h practice).

Each intervention (SP, MHL and MHL + SR) will be delivered to students during a tutorial class (one hour/week) and will be supported by Prezi-format presentations (https://prezi.com) about the 6 modules of the EspaiJove.net programme. Table 1 shows the contents of the EspaiJove.net programme among the different intervention groups.

**Table 1 Tab1:** Contents of the EspaiJove.net programme in the different intervention groups

Hour	Workshop Contents	SP (1 h)	MHL (6 h)	MHL + SR (7 h)	Comparison group
1	Concepts of mental health (MH) and mental disorders (MD). Emotional management	x	x	x	Waiting List
2	Healthy and risk behaviours in MH		x	x	
3	Social skills and antisocial behaviours, bullying and cyberbullying		x	x	
4	Anxiety, depression and self-harm and suicidal behaviours		x	x	
5	Eating and behavioural disorders		x	x	
6	Substance abuse. Psychotic disorders		x	x	
7	Stigma Self-experience in MD and MH presentation of an activist of a voluntary member of Activament Catalunya Associació (http://www.activament.org/es)			x	

Abbreviations: *SP* Sensitivity Programme, *MHL* Mental Health Literacy Programme, *HML + SR* Mental Health Literacy Programme plus Stigma Reduction

Students from the control schools will act as a waiting list, and they will receive the MHLP +SR (7 h) programme after 12 months follow up, thus during the next academic year of 2018–2019.

### Recruitment process

The recruitment process for the trial began in September 2016. All eligible secondary schools within Barcelona city are contacted and encouraged to participate in the study. Emails providing information about the study are sent to all schools, and among those schools that had shown an interest in participating, a presentation is delivered at the school by two project researchers. Once a school agreed to participate, consent letters are sent out to the parents of all participating students.

Out of all the schools that accept participation in the study, a cluster randomisation by school and individual students as participants is conducted. The total sample estimated within a minimum of 408 adolescents will be divided into three experimental groups and one control waiting list. The randomisation assignment will be carried out through a computer program, and the group assignment will be 1:1:1:1.Each interviewer blinded the assessments.

Pre-treatment questionnaires will be completed approximately 2 weeks before the intervention by all students (intervention and control groups). A code will be used to match participant answers over time whilst preserving anonymity. One teacher will be the unique person responsible for keeping the identification number and corresponding student. Two researchers will be responsible for supplying each student with a questionnaire for its completion during each assessment within the study. The class teacher will be present in the classroom during the questionnaire administration involved in the data collection with the aim of minimising missing data and errors when providing the questionnaires.

A second evaluation will be performed approximately 2 weeks after the intervention. A third and fourth evaluation will be examined at 6 and 12 months, respectively. Table 2 shows the data collection and intervention programme timelines.

**Table 2 Tab2:**
[figure not shown]
Data collection and intervention programme timeline

An Informed Consent Form (for children and parents) will be required for all participants prior to their involvement in the study. The confidentiality of the participants (children) will be protected using an encryption key for any personal details within the data (school 1–8, class 1–6, identification number 1–34). The key will be stored separately. Ethical approval was granted by the Fundació Unió Catalana Hospitals.

### Measures

The variables and instruments selected, as well as the evaluation programme timeline, are detailed in Table 3. Collected data will then be imported using a teleform format program onto a computer database.

**Table 3 Tab3:** Outcome measures

Outcome measures	Timeline			
	Pre-intervention	Post-intervention		
		2 w	6 mo	12 mo
Primary outcomes				
1. Mental Health Knowledge				
EspaiJove.net Mental Health Literacy Questionnaire (EMHLQ)	X	X	X	X
2. Behaviour and Attitudes Towards Mental Health (Stigma)				
Reported and Intended Behaviour Scale (RIBS)	X	X	X	X
The Scaling Community Attitudes toward the Mentally III (CAMI) - Authoritarianism subscale	X	X	X	X
Others outcomes				
3. Acceptability and satisfaction				
Satisfaction questionnaire		X		
4. Mental Health Symptoms and Emotional Well-Being				
Strengths and Difficulties Questionnaire (SDQ)	X	X	X	X
5. Bullying and Cyber-Bullying Behaviours				
Bullying and Cyber-Bullying Questionnaire	X	X	X	X
6. Intentions to Change				
Intentions to Change Questionnaire (ICQ)	X	X	X	X
7. Health-related quality of life				
EuroQol Questionnaire (EQ-5D-5 L)	X	X	X	X
8. Help-seeking				
General Help-Seeking Questionnaire (GHSQ)	X		X	X
9. Use of Health Services and Treatment				
Use of Health Services and Treatment questionnaire	X		X	X
10. Health Benefits Questionnaire				
Familiar, academic and general health questions	X		X	X

*Abbreviations*: *mo* months, *w* weeks

First of all, socio-demographic variables will be collected: age; date of birth; gender; nationality; city/village; neighbourhood of residence or postcode. The following variables are listed below:

### Primary outcomes

The primary outcomes of this study are mental health literacy (MHL) and stigma associated with mental illness.

### Mental health knowledge

***EspaiJove Mental Health Literacy Test (EMHLT)*** is a self-reported questionnaire based on the thematic contents of the EspaiJove.net school programme. The EMHLT consist of 35 items, it uses two response formats: (i) the first part consists of a binary choice format (yes/no) for the recognition of mental disorders from a list of 15 different diseases; (ii) the second part contains 20 multiple choice questions with four possible answer options, in which only one is correct. To obtain the score for each individual in the test, the formula (A-E)/(n-1) is used, where A = the number of correct answers, E = the number of errors, and n = the number of options for each item. Thus, for section one of the test, the formula would be (A-E)/(2–1); and for the second part (A-E)/(4–1), where each correct answer adds one point to the total score. The total score of the test would be the result of the addition of both sections and would vary between 0 and 35 points. The cut-off point selected (pass test) was 25 points, representing approximately 70% of the answers [33].

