### Statistical analysis

To analyse the effectiveness of the EspaiJove.net intervention, an experimental design will be created to evaluate the programme, randomised by clusters (schools) and with a control group on the waiting list. The statistical analyses to be performed will be as follows. A description of the sociodemographic variables of the sample at baseline will be done through a univariate analysis of the selected variables from the total sample and stratified by type of intervention. Then, to evaluate the effectiveness of all programmes and to achieve statistical significance for all outcomes after the intervention, an unadjusted bivariate primary analysis will be performed. Data scores after the intervention will be analysed with ANOVA, assuming that the baseline data will be similar due to the randomisation process across groups. Finally, a multivariate and adjusted analysis, as necessary, will be employed to evaluate the effectiveness of those programmes so as to achieve statistical significance after the intervention. Data will be analysed with Generalised Equation Estimates (GEE) to assess the efficacy of the intervention. This statistical model is appropriate for longitudinal clustering analyses since this study design (schools) will allow us to consider the individual data correlation within the same cluster group. Analyses will be based on an intention-to-treat analysis.

We will also examine relative and absolute risk reduction, (RRR) and (ARR), respectively. Additionally, to analyse the acceptability and satisfaction of each programme, a descriptive analysis will be performed to observe the percentage of acceptability and satisfaction. Statistical analyses will be performed using the SPSS [48].

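### The printed EMHLT scoring formula tops out at 21.67, so it contradicts the stated 0–35 range, the one point per correct answer and the 25-point pass mark

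*Protocol article*

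**What the plan says.** All of the scoring material is in the Mental health knowledge section of the protocol article.

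- Structure: "The EMHLT consist of 35 items, it uses two response formats". The first is a "binary choice format (yes/no) for the recognition of mental disorders from a list of 15 different diseases"; "the second part contains 20 multiple choice questions with four possible answer options, in which only one is correct".
- General rule: "the formula (A-E)/(n-1) is used, where A = the number of correct answers, E = the number of errors", with n the number of options per item.
- Rule for each part: "the formula would be (A-E)/(2–1); and for the second part (A-E)/(4–1), where each correct answer adds one point to the total score".
- Range: "The total score of the test would be the result of the addition of both sections and would vary between 0 and 35 points". The pass mark is 25, which the section equates with roughly 70% of the test.

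The Primary outcomes section and Table 3 list mental health literacy as a primary outcome. The Statistical analysis section compares scores by ANOVA and then by GEE. It adds: "We will also examine relative and absolute risk reduction, (RRR) and (ARR), respectively". No other section gives a different scoring rule.

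**The concern.** The formula divides the whole difference A − E by n − 1. In the four-option part this shrinks the credit for correct answers as well as the penalty for errors. A penalty that makes blind guessing worth zero on average needs the divisor under E only. As printed, the formula cannot produce the range, the item weight or the pass mark given beside it.

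This is the only scoring rule shown for a primary outcome. Someone who codes it literally obtains a different variable from one who works back from the 0–35 range, and the two are not linear rescalings of each other, because only the second part is compressed.

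**Working it through.** **Inputs** (all from Mental health knowledge): part one has 15 items with n = 2; part two has 20 items with n = 4; A = correct, E = errors; stated range 0 to 35; pass mark 25.

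**1. Trying to reproduce the stated range with the printed rule.**
- Maximum: (15 − 0)/1 + (20 − 0)/3 = 15 + 6.67 = 21.67, not 35.
- Minimum: (0 − 15)/1 + (0 − 20)/3 = −21.67, not 0.
- One correct answer in part two, compared with a blank: 1/3 point, not 1.
- All 31,416 combinations of correct, wrong and blank counts (136 for part one × 231 for part two) were scored. None reaches 25.

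**2. Two candidate rules that give a maximum of 35.**

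| | Printed (A−E)/(n−1) | A − E/(n−1) | Plain count of A |
|---|---|---|---|
| Maximum | 21.67 | 35 | 35 |
| Minimum | −21.67 | −21.67 | 0 |
| Credit per correct answer, part two (vs blank) | 1/3 | 1 | 1 |
| Mean from pure guessing, part two (5 right, 15 wrong) | −3.33 | 0 | 5 |
| Can 25 be reached? | No | Yes (419 of 31,416 combinations) | Yes |

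On a 35-point scale, 25/35 = 71%, which agrees with the section's description of the cut-off. On the printed scale, 25 exceeds the maximum.

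**3. Weight of part two when every item is answered.** Put E = 15 − A in part one and E = 20 − A in part two.
- Part one is 2A − 15 under the printed rule and under A − E/(n−1): 2 points per extra correct answer, spread 30.
- Part two as printed is (2A − 20)/3: 2/3 point per extra correct answer, spread 13.33.
- Part two under A − E/3 is (4A − 20)/3: 4/3 points per extra correct answer, spread 26.67.

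Part two's weight relative to part one is therefore (2/3)/2 = 1/3 as printed and (4/3)/2 = 2/3 under the correction, so it is halved. Its share of the attainable spread is 13.33/43.33 = 31% as printed and 26.67/56.67 = 47% under the correction.

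**4. Two worked papers, all items answered.**
- 13/15 and 16/20 correct. Printed: (13 − 2) + (16 − 4)/3 = 15.0. A − E/(n−1): 11 + (16 − 4/3) = 25.67, a pass. Plain count: 29, a pass.
- 11/15 and 14/20 correct, which is 25 of 35. Printed: 7 + 8/3 = 9.67. A − E/(n−1): 7 + (14 − 2) = 19, a fail. Plain count: 25, a pass.

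The second paper shows that the meaning of the 25-point cut-off depends on which rule it was derived under.

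**The case against.** The best defence is that this is a notation slip in a condensed article. The 35-point range and the 25-point cut-off suggest that the investigators work on a 35-point scale, and their scoring code may already be right. That is plausible, and it makes the practical harm conditional on the printed rule being coded. It does not remove the contradiction: the formula appears in general form and again with numbers for both parts, each time with the whole difference in brackets, so an extraction fault is unlikely.

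A second objection concerns the remedy. A − E/(n−1) is nowhere in the article, and the source it cites for the test is not available here. A plain count of correct answers also gives one point per answer and 0 to 35, and it gives the lower bound of 0 without a further rule. This stands: the standard correction is the stronger inference because it uses the same A, E and n, but it needs confirmation.

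A third objection concerns the consequences. Within part two, with all items answered, both rules are linear in A, so pupils rank identically there. The lower score for guessing is then a change of location and scale within that part. What remains is the change in weight between the two parts. This also stands.

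**Conclusion.** The scoring rule is wrong as written: its range of −21.67 to 21.67 cannot be reconciled with the three statements beside it. This follows by arithmetic from one section and needs no outside assumption. If the rule were coded literally, the pass rate would be zero in every arm, and part two would carry 31% of the attainable spread instead of 47%. The 47% assumes that A − E/(n−1) is the intended rule and that all items are answered.

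Four stronger readings are tempting but not supported:
- *Arm comparisons are biased.* The same rule applies to every arm. It reweights the outcome, and so may change the size of an observed difference, but nothing shows that it favours one arm.
- *The risk reductions become zero or undefined.* The Statistical analysis section does not say which variable RRR and ARR use. The consequence arises only if they are computed on the pass mark.
- *The sample size is invalidated.* It rests on a standardised effect of 0.18 and does not depend on the score range.
- *Part two falls from 57% to 31%.* The 57% is 20/35, its share of the maximum. It is not the share of spread under the guessing correction, which is 47%.

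**What to change.** 1. Check the intended rule against the instrument's source and the scoring code. If confirmed, replace the printed formula with A − E/(n−1) per part: A − E for part one and A − E/3 for part two. If the source uses a plain count of correct answers, print that and delete the formula.
2. State the true range. Under the guessing correction it is −21.67 to 35, or 0 to 35 with an explicit rule that negative totals are set to 0.
3. Confirm that the 25-point pass mark was derived on the scale adopted.
4. If RRR and ARR are meant to use the pass mark, say so.

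All of this should be settled before any data are scored. The cost is one corrected formula, a sentence or two of text and a check of the scoring code; no new data are needed.
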